## Design synopsis

---

### Title

- Pilot Study of the Safety, Feasibility, and Potential Efficacy of Continuous Glucose Monitoring and Insulin Pump Therapy in Diabetic Gastroparesis (GLUMIT-DG)

### Sponsor

- National Institute of Diabetes and Digestive and Kidney Diseases

### Type of study

- Multicenter, uncontrolled, open label treatment
- Safety and feasibility

### Objective

- To assess the safety, feasibility, and potential (uncontrolled) efficacy of real-time continuous glucose monitoring (RT-CGM) as an adjunct to self monitoring blood glucose (SMBG) in guiding insulin pump therapy to improve glycemic control for treatment of type 1 or type 2 diabetic patients with gastroparesis

### Population

- Patients aged 18 - 70 years old at registration with mild to moderate symptoms of gastroparesis for at least one year and a diagnosis of type 1 or type 2 diabetes mellitus for at least 2 years.

### Study duration – per patient

- A minimum of 4 weeks and up to 16 weeks of screening and baseline assessments prior to enrollment
- 24 weeks of open label treatment and follow-up after enrollment

### Sample size and statistical analysis of primary outcome

- A total of 40 patients will be enrolled in this pilot study
- Rationale for sample size
  - Primary safety outcome: weekly frequency of mild, moderate, or severe hypoglycemic episodes by discrete glucose meter values and/or a reference blood glucose level if the subject is seen in a hospital (emergency room)
  - Assumed mean weekly mild, moderate, or severe hypoglycemic episodes by discrete glucose values: 0.6
  - Assumed SD for weekly mild, moderate, or severe hypoglycemic episodes by discrete glucose values: 0.8
  - Assumed intra-class correlation between baseline and on-treatment weekly mild, moderate, or severe hypoglycemic episodes by discrete glucose values: 0.6
  - Estimated variance of change from baseline (a minimum of 4 weeks up to 16 weeks) to on-treatment (24 weeks) mean weekly mild, moderate, or severe hypoglycemic episodes (estimated from SD and intraclass correlation, accounting for 3:1 ratio of on-treatment to baseline period lengths): 0.41
  - Type I error: 0.05 (1-sided for equivalence)
  - Power: 0.9
  - Expected percent increase from baseline in mean weekly mild, moderate, or severe hypoglycemic episodes during the treatment period with RT-CGM while using the

- glucose pump: 0%
- Equivalence limit (maximum percent increase in mean weekly mild, moderate, or severe hypoglycemic episodes): 35% (0.6 vs. 0.81 episodes per week)
- Method for sample size calculation: One sample test for equivalence (Chow, Shao and Wang, Sample Size Calculations In Clinical Research, Taylor & Francis, NY, 2003: p. 52-53)
- Software: Centre for Clinical Trials, Chinese University of Hong Kong -- [http://www.cct.cuhk.edu.hk/stat/mean/osm\\_equivalence.htm](http://www.cct.cuhk.edu.hk/stat/mean/osm_equivalence.htm)
- Calculated sample size: N = 37

**Number of clinical centers**

- 7 (two lead clinics and 5 additional clinical sites added later)

**Inclusion criteria**

- Age 18 - 70 years old at registration
- Type 1 or Type 2 diabetes mellitus for at least 2 years
- Symptoms of gastroparesis (nausea, vomiting, early satiety, bloating, fullness, discomfort) for at least 1 year prior to registration with a Gastroparesis Cardinal Symptom Index (GCSI) score of  $\geq 18$
- Delayed gastric emptying on gastric scintigraphy within 1 year of registration, defined as greater than 60% retention at 2 hours or greater than 10% retention at 4 hours
- Hemoglobin A1c of at least 8.0% at registration with current therapy indicating the need for insulin therapy. Individuals already receiving diabetes therapy via an insulin pump will be eligible for study participation if, in the opinion of the investigators, he/she may acquire additional benefit from continuous glucose monitoring that might improve glycemic control
- Normal upper endoscopy within 1 year of registration
- No clinical or imaging evidence of obstruction
- Successful mastering of use of RT-CGM during the run-in period

**Exclusion criteria**

- Prior gastric surgery including fundoplication
- Other systemic disease potentially causative of gastrointestinal symptoms
- Acute or chronic renal insufficiency with creatinine  $>1.5$  mg/dL
- Current psychiatric disease or eating disorder
- Pregnancy
- Any other condition which, in the opinion of the investigators, would impede compliance or hinder completion of the study

**Outcome measures**

- **Primary:** The primary outcome measure is defined as the frequency and extent of mild or moderate hypoglycemic episodes (defined as a capillary glucose level less than 70 mg/dL documented by the home glucose meter and/or a reference blood glucose level if the subject is seen in a hospital (emergency room) setting and absolute number of severe hypoglycemic episodes recorded at the 12 and 24 week follow-up visits while subjects are using a combination of RT-CGM and insulin pump therapy.
- **Secondary outcome measures** will be defined to address the following:  
Effects of RT-CGM and insulin pump therapy on:
  - Hemoglobin A1c at baseline, 12, and 24 week follow-up visits

- 
- Percent time of day in hypoglycemia (<70 mg/dl), euglycemia (70-180 mg/dl), or hyperglycemia (>180 mg/dl) as determined by capillary glucose measurements and in a separate analysis by RT-CGM
  - Glycemia variability (blood glucose rate of change) based on RT-CGM readings
  - Hyperglycemia index and hypoglycemic index using capillary glucose -measurements in one analysis and RT-CGM in a separate analysis
  - Gastroparesis patient-related outcome measures using the GCSI, PAGI-SYM and -PAGI-QOL scores at baseline, 12, and 24 week follow-up visits
  - Maximal volume of water and Ensure consumed during satiety tests at baseline, 12, and 24 week follow-up visits
  - Percent tachygastria, bradygastria and normal 3 cycles per minute (cpm) activity during electrogastrogram (EGG) and satiety testing at baseline, 12, and 24 week follow-up visits
  - Vagal cholinergic and sympathetic adrenergic functions at baseline, 12, and 24 week follow-up visits

**Recruitment**

- 20 type 1 and 20 type 2 diabetics with gastroparesis will be enrolled at 7 clinical centers
- 30 month period
- Enrollment of 10 patients at the Wake Forest University clinical center
- Enrollment of 5 patients per clinical center expected at the remaining 6 clinical centers

**Duration of open label treatment and follow-up**

- 24 weeks

**Visit schedule**

- Screening into the study: enrollment should occur within 16 weeks of registration
  - During the baseline assessment, prospective participants will learn how to use an iPro sensor to obtain retrospective CGM data
  - If subjects are successful in using the iPro, they will receive training in RT-CGM and in insulin infusion pump therapy. They will be taught how to use the trend analysis from RT-CGM as adjunctive information to home glucose monitoring measurements in making insulin dose decisions.
- Run-in visits: At least 4 visits to receive training on use of an insulin pump in conjunction with RT-CGM.
- Treatment and follow-up phase: Every 4 weeks after enrollment throughout the 24 week open label treatment study

**Safety monitoring**

- The NIDDK-appointed DSMB will perform interim monitoring of the accumulating GLUMIT-DG study data for patient safety and potential (uncontrolled) efficacy according to the Data and Safety Monitoring Plan (DSMP) for the GLUMIT-DG study.
  - The DSMB will review safety data only when approximately N=10 patients have completed the study. The DSMB will advise on whether or not it is safe to proceed towards the full sample size of 40 patients
-

## 1. Objectives

---

The principal objective of this multicenter, uncontrolled, open label treatment study is to assess the safety of RT-CGM as an adjunct to self monitoring blood glucose (SMBG) in guiding insulin pump therapy for 24 weeks by measuring mild, moderate, and severe hypoglycemic episodes in patients with type 1 or type 2 diabetes and gastroparesis.

Other objectives include:

- To determine the feasibility of achieving improved glycemic control with RT-CGM as an adjunct to SMBG-guided insulin pump therapy in patients with diabetes and gastroparesis.
  - To determine the efficacy of RT-CGM as an adjunct to SMBG-guided insulin pump therapy for 24 weeks as measured by improvements in symptoms of gastroparesis, gastroparesis-related quality of life, satiety, gastric myoelectrical activity, and autonomic function in diabetics with gastroparesis.
-

## 2. Background and Significance

---

### 2.1 Introduction

Gastroparesis is a disorder of gastric neuromuscular sensory and motor function that affects patients in the prime of their life. Gastroparesis is a devastating disease affecting predominantly young women (females outnumber males by a ratio of 4:1, with an average 34 years of age). The symptomatic profile of gastroparesis includes nausea (90% of patients), vomiting (>80%), pain (~50%), early satiety (60%), and bloating (75%) and can vary in both the combination of symptoms and their severity. Because of its chronic and often intractable nature, the disorder has a tremendous impact on both patients and society at large. Gastroparesis remains difficult to treat, in large part because of the lack of knowledge of the underlying pathophysiology of this disease. Several factors, in particular, have impeded the progress in this field including the paucity of patients seen by any one center, the absence of uniform diagnostic criteria, the lack of generally available, reliable methods for physiological testing and the inaccessibility of tissue for histopathological correlation.

The Gastroparesis Clinical Research Consortium (GpCRC) is a cooperative network of seven clinical centers and one Data Coordinating Center (DCC) supported by the National Institute of Diabetes and Digestive and Kidney Diseases (NIDDK), through the mechanism of RFA-DK-05-004, established in 2006. Clinical centers are responsible for proposing protocols, participating in their overall development, recruiting patients, conducting the research, and disseminating research findings. The individual clinical centers participate in a cooperative and interactive manner with one another and with the DCC in all aspects of the GpCRC. The DCC supports protocol development; provides sample size calculations, statistical expertise, forms, and data analysis; supports manuscript preparation; and provides overall study coordination and quality assurance, including coordination of the activities of the Data and Safety Monitoring Board, the Steering Committee and other standing committees.

### 2.2 Diabetic gastroparesis

It is well established in the literature that optimal control of blood sugar in patients with long-standing diabetes mellitus slows the progression of several of the systemic complications of the disease, including peripheral neuropathy and renal disease. Gastrointestinal manifestations are prevalent in individuals with diabetes, especially in those who have had poorly controlled disease for 10 or more years. Nausea, vomiting, fullness, early satiety, bloating, discomfort, and altered glycemic control represent the symptoms of diabetic gastropathy. Many individuals with diabetic gastropathy exhibit delays in gastric emptying of solid meals and are considered to have gastroparesis. However, studies of the effects of hyperglycemia on gut function have been limited to acute settings in which some parameter of muscular, myoelectrical, or sensory function is modulated by acute experimental changes in blood glucose.

In diabetics, induction of hyperglycemia slows both solid and liquid phase gastric emptying, blunts phasic antral contractions, and leads to generation of gastric slow wave dysrhythmias such as tachygastria. In healthy non-diabetic volunteers, acute hyperglycemia also induces tachygastria and blunts antral contractility. Acute hyperglycemia also increases gastric sensitivity to mechanical stimulation, and reduces responses to prokinetic drugs. On the basis of these acute studies, gastroenterologists routinely recommend optimal glycemic control to minimize gastrointestinal consequences of poorly controlled diabetes. However to date, there remains no hard data from well-controlled, long-term trials to validate this recommendation.

### 2.3 REAL-Time Continuous glucose monitoring system (RT-CGM)

Recently, commercially available continuous glucose monitors have become available to track interstitial glucose levels in real time in patients with diabetes. This method has significant potential to enhance glycemic control in diabetics with frequent hypoglycemic events. Indeed, continuous monitoring detects a

high number of unsuspected hypoglycemic events which are unrecognized by the patient with the traditional finger stick method. Furthermore, this method has been shown to reduce mean hemoglobin A1c values by 0.4% within a 12-week period. From a safety standpoint, continuous glucose monitoring increases the detection rate of nocturnal hypoglycemia in type 1 diabetics.

This study will determine the safety, feasibility, and potential efficacy of using a Real-Time continuous glucose monitoring system (RT-CGM) as an adjunct to capillary glucose measurement to guide insulin pump therapy in patients with type 1 or type 2 diabetes complicated with gastroparesis. Along with the measurement of interstitial glucose concentrations using the RT-CGM, patients in this study will be instructed to perform measurements of blood glucose levels four times daily using a finger stick method with a glucose meter. Throughout GLUMIT-DG Study, patients will be provided with the One Touch® UltraLink or Bayer CONTOUR® Next Link blood glucose meter for self monitoring blood glucose (SMBG) measurements to guide insulin pump therapy. The finger stick blood glucose (SMBG) results will be used for calibration of the RT-CGM and also for glucose monitoring as a guide for insulin therapy. The results from the blood glucose meter will be used to guide insulin infusion with a continuous subcutaneous insulin infusion system (insulin pump).

The RT-CGM system consists of three main components:

- **Glucose sensor:** monitors the interstitial glucose glucose;
- **MiniLink REAL-Time Transmitter:** sends glucose readings from the sensor to the insulin pump; and
- **Insulin pump:** displays and receives glucose readings.

#### 2.4 Insulin pump

Along with the use of the RT-CGM, patients will use the insulin pump to achieve optimal blood glucose control. Depending on availability the patients will use the MiniMed Paradigm® Model 722 or MiniMed Paradigm® Revel Model 723 insulin pump. The rate of basal insulin infusion and the amount of insulin for meals as well as any extra amount of insulin needed for a glucose reading that exceeds 180 mg/dL will be adjusted using blood glucose measurements obtained from the glucose meter. Participants will receive extensive training on the use of both RT-CGM and the insulin pump which will replace the current diabetes treatment. Optimization of insulin pump treatment will take place for those who are already using an insulin pump prior to GLUMIT-DG registration. The parameters of the pump will initially be programmed according to parameters based on the patient's type of diabetes, food intake, and body weight. Special precautions will be built into bolus insulin administration for meals since all patients will have gastroparesis.

---

### 3. Study Design

#### 3.1 Design overview

GLUMIT-DG is a multicenter, uncontrolled open label treatment study assessing the safety, feasibility, and potential efficacy of RT-CGM as an adjunct to self monitoring blood glucose (SMBG) in conjunction with insulin pump therapy for patients with type 1 or type 2 diabetes and gastroparesis. Participants will include patients enrolled in GpCRC studies (e.g., Gastroparesis Registry, Gastroparesis Registry 2 Study) qualifying for GLUMIT-DG and other patients with diabetes and gastroparesis referred to study physicians, or patients from the investigators' clinics. Twenty patients with type 1 diabetes and twenty patients with type 2 diabetes will be enrolled into GLUMIT-DG study. Screening for eligibility, collection of baseline data, iPro CGM training for baseline glycemic assessments, and the run-in period for real-time continuous glucose monitoring (RT-CGM) training with the insulin pump will span up to 16 weeks after obtaining informed consent for participation in the study. After successful completion of the run-in period, patients will be enrolled in the study and use RT-CGM coupled with insulin pump therapy to optimize glucose levels while determining the frequency of hypoglycemic events for 24 weeks. After study completion, patients will be given the option of returning to or participating in the Gastroparesis Registry 2 Study. A schematic of the study design is presented below:

### GLUMIT-DG Study Design

[figure not shown]

- Multicenter, uncontrolled, open label treatment study
- Continuous Glucose Monitoring System and Insulin Pump Therapy

The primary outcome measure of GLUMIT-DG relates to the safety (hypoglycemic episodes) when using RT-CGM as an adjunct to self monitoring blood glucose (SMBG) to guide insulin pump therapy in patients with diabetes and gastroparesis. Secondary analyses will include: the effects of the use of RT-CGM as an adjunct to self monitoring blood glucose (SMBG) to guide insulin pump therapy on hemoglobin A1c levels, glycemic variability (blood glucose rate of change) based on RT-CGM readings, hyperglycemic index and hypoglycemic index using capillary glucose measurements in one analysis and RT-CGM in a separate analysis, Patient Assessment of Upper Gastrointestinal Disorders- Symptoms (PAGI-SYM), Patient Assessment of Upper Gastrointestinal Disorders- Quality of Life (PAGI-QOL) scores, maximal volume of water and caloric drink consumed during satiety tests, percent tachygastria during electrogastrogram (EGG), and vagal cholinergic and sympathetic adrenergic functions.

### 3.2 iPro™ training through the screening period

Patients will initially be instructed by the diabetologist and the diabetes educator on use of the iPro Continuous Glucose Monitor System (CGMS). Patients will then use the iPro CGM or iPro2 CGM for a period lasting at least 2 weeks (or potentially 4 weeks depending on a patient's performance level) to obtain baseline glycemic data. Patients will measure their blood glucose levels 4 times daily using a standard finger stick method (SMBG) with a glucose meter. Depending on availability, patients will be provided with the One Touch® UltraLink or Bayer CONTOUR® Next Link blood glucose meter. Data obtained from the iPro CGM during this training period will not be seen by the patient and will not be used for diabetes management. A successful iPro CGM training period will be defined as the acquisition of continuous recording of glycemic data, in addition to self monitoring of blood glucose (SMBG), for at least 216 hours (9 days) or greater during a 2 week period. If patients cannot successfully master the iPro CGM and collect the required duration of data, they will be offered an additional 2 week period to demonstrate proficiency in the use of iPro CGM to collect the sufficient amount of data (216 hours or more). If the patient is again unsuccessful, he/she will be considered a screen failure and will not be enrolled in the study. Along with showing iPro proficiency, patients must perform 4 blood glucose tests (SMBG) daily, as another indicator of proficiency and compliance in order to continue in the screening phase of the study. Additionally, patients with type 1 diabetes will also be trained on the use of serum ketone meters.

The following additional glycemic data will be calculated from the iPro CGM prior to enrollment in the GLUMIT-DG study:

- Percent time of the day during which prevailing glucose levels are within euglycemic boundaries (80-180 mg/dL).
- Low blood glucose index (LBGI) reflecting the frequency and extent of hypoglycemic episodes.
- High blood glucose index (HBGI) reflecting the frequency and extent of hyperglycemic episodes.
- Glycemia variability standard deviation of blood glucose rate of change.
- Number of episodes of hypoglycemia (glucose <70 mg/dL, mild or severe) per week recorded by the iPro CGM, but not captured by the standard finger stick approach.

Subsequent to the screening period, the patients will undergo up to 8 weeks of a run-in phase in which they will learn to operate the MiniLink™ REAL-Time Transmitter Continuous Glucose Monitoring System (RT-CGMS) which is similar to the iPro CGM coupled with the insulin pump.

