### 5.1 Visit schedule overview

The patient-related activities of the GLUMIT-DG study can be divided into 3 phases:

- **Screening Phase:** Screening to determine eligibility and receive training on the use of an iPro which is a CGM used for retrospective analysis of CGM results. While wearing the device the subject is blinded to their sensor glucose values. This period is so that the subjects can demonstrate a willingness to wear a sensor, gain proficiency in inserting a sensor, and provide the study baseline data of their CGM readings (retrospectively). This will occur over 2-8 weeks and include 2 visits for gastric related testing as well as iPro training. To progress in the study the subject will need to have at least 216 hours of iPro readings.
- **Run-in Phase:** Initiation of insulin pump training and training in the use of real-time CGM (4 visits over a minimum of 2 weeks up to a maximum of 8 weeks)
- **Follow-up Phase:** Study treatment to assess the safety of using RT-CGM as an adjunct to SMBG-guided insulin pump therapy over 24 weeks (6 visits)

The visit and data collection schedule described below in detail is summarized in Appendix 10.2

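### Percent time in euglycemia is defined as 80-180 mg/dL for the iPro baseline and 70-180 mg/dL for the secondary outcome; a sensor comparison built on both would be biased toward improvement

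*Protocol*

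**What the plan says.** Section 3.2 of the protocol says that patients wear the iPro for at least two weeks "to obtain baseline glycemic data". It then introduces a list of derived variables: "The following additional glycemic data will be calculated from the iPro CGM prior to enrollment in the GLUMIT-DG study". The first item is "Percent time of the day during which prevailing glucose levels are within euglycemic boundaries (80-180 mg/dL". The last item in the same list counts hypoglycemic episodes with a cut-off of <70 mg/dL. Section 5.1 says that the screening phase is there, among other reasons, to "provide the study baseline data of their CGM readings (retrospectively", and section 3.1 also ties iPro wear to the baseline glycemic assessment.

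The synopsis, under Outcome measures, opens the secondary outcomes with "Effects of RT-CGM and insulin pump therapy on" and includes "Percent time of day in hypoglycemia (<70 mg/dl), euglycemia (70-180 mg/dl), or hyperglycemia (>180 mg/dl", to be analyzed "as determined by capillary glucose measurements and in a separate analysis by RT-CGM".

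Section 8.2 lists the same secondary outcome without boundaries. Its account of the CareLink software also leaves the euglycemic range unnumbered, so it does not settle which range applies.

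**The concern.** One quantity, percent of the day in euglycemia, has two lower bounds: 80 mg/dL in the iPro baseline list and 70 mg/dL in the outcome definition. A reading of 75 mg/dL is outside euglycemia under the first and inside it under the second.

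The study has no control group, so an effect of treatment on time in euglycemia can be read only as a within-patient change. If the baseline value comes from section 3.2 and the on-treatment value from the synopsis, part of the change is created by the definitions. The direction is fixed, because the wider range is the one applied on treatment. Section 8.3 says that the pilot is meant to supply effect sizes and variability for a later randomized trial, so an overstated change could also enter that trial's planning.

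**Working it through.** The protocol states no expected value, power or margin for this outcome, so there is no figure of its own to reproduce. The check covers the direction of the error, then its possible size.

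**Inputs**
- Baseline range 80-180 mg/dL: section 3.2.
- Outcome range 70-180 mg/dL: synopsis, Outcome measures.
- Share of time at 70-79 mg/dL: not in the protocol. Assumption: glucose is lognormal with mean 150, 180, 210 or 240 mg/dL and CV 30% to 50%. The entry requirement of HbA1c at least 8.0% (section 4.2) serves only as a reason to expect a high mean.

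**Direction**

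Write B for the baseline proportion of time and T for the on-treatment proportion. The range 70-180 contains 80-180, so B(80-180) = B(70-180) − B(70-79), and

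T(70-180) − B(80-180) = [T(70-180) − B(70-180)] + B(70-79).

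The bracket is the real change on the outcome definition. The last term is the artefact. It is a proportion of time, so it cannot be negative. If nothing changes, the bracket is zero and the apparent gain equals B(70-79).

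**Size**

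For mean m and coefficient of variation CV, σ² = ln(1 + CV²) and μ = ln m − σ²/2. The artefact is Φ((ln 80 − μ)/σ) − Φ((ln 70 − μ)/σ).

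Example with m = 180 and CV = 40%:
- σ² = ln 1.16 = 0.1484, so σ = 0.3853 and μ = 5.1930 − 0.0742 = 5.1188.
- The standardized limits are (4.3820 − 5.1188)/0.3853 = −1.91 and (4.2485 − 5.1188)/0.3853 = −2.26.
- The artefact is 0.0279 − 0.0119 = 0.0160, or 1.6 points. Time in euglycemia reads 54.8% with 80-180 and 56.4% with 70-180, from the same glucose distribution.

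Spurious gain in percentage points with no true change:

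| Mean (mg/dL) | CV 30% | CV 35% | CV 40% | CV 45% | CV 50% |
|---|---|---|---|---|---|
| 150 | 1.59 | 2.74 | 3.80 | 4.64 | 5.26 |
| 180 | 0.34 | 0.88 | 1.60 | 2.35 | 3.04 |
| 210 | 0.07 | 0.27 | 0.65 | 1.15 | 1.71 |
| 240 | 0.01 | 0.08 | 0.26 | 0.56 | 0.95 |

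The largest value in the table is 0.0526 × 24 = 1.3 hours a day. The largest at a mean of 180 or more is 0.0304 × 24 = 0.7 hours a day.

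**After the correction**

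With one range in both periods the artefact term disappears, and the change is exactly 0 when the glucose distribution does not change.

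**The case against.** The strongest reply is that the protocol never writes down the comparison that would be biased. It gives no change-from-baseline formula for this outcome. The synopsis does not restrict 70-180 to the treatment period, and it names capillary values and RT-CGM as sources, not iPro. Section 3.2 presents its figure as supplementary pre-enrollment data. Section 3.3 also speaks of baseline RT-CGM data from the run-in. An RT-CGM-to-RT-CGM or meter-to-meter comparison would never meet the 80 mg/dL bound, and an SAP may define the derivation with a single range.

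Much of this stands. A reader might infer that the reported change must show an improvement even if nothing changes. The text supports only the conditional statement: it will if the section 3.2 figure is used as the baseline for the RT-CGM outcome. What the reply does not remove is the contradiction. The protocol fixes both ranges itself, and it describes the iPro recordings as baseline in three places. The section 3.3 mention of run-in data concerns setting pump parameters for patients already on pumps. An SAP that took section 3.2 literally would carry the error forward.

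Three other inferences should be resisted:
- **Baseline categories that fail to sum to 100%.** Section 3.2 defines only one percent-time variable, alongside risk indices, a variability measure and an episode count. Readings of 70-79 mg/dL are neither hypoglycemic nor euglycemic there, but no set of percentages was meant to add up.
- **A leading outcome.** It is one of several secondary outcomes. The list of secondary analyses in section 3.1 leaves percent time out, and section 8.3 singles out HbA1c as the important secondary efficacy outcome.
- **A substantial distortion in every patient.** At the higher mean glucose values that the entry HbA1c suggests, the artefact can be close to zero.

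**Conclusion.** The protocol contradicts itself on the euglycemic range. That part is certain. The bias is conditional: it arises if the iPro figure serves as the sensor baseline and both ranges are applied as written. It then always favors the treatment and equals the baseline share of time at 70-79 mg/dL.

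That share is unknown. Under the lognormal assumption it runs from about 0 to 5 percentage points over means of 150-240 mg/dL and CVs of 30-50%, and from 0 to 3 points at means of 180 mg/dL or more. Given the HbA1c entry criterion, the lower part of the range is more plausible on average; patients with lower or more variable glucose would show more.

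The exposure is limited to the sensor analysis of one secondary outcome. No 80-180 range is stated for capillary percent time, and neither the primary outcome nor the sample size uses this variable. The point is modest in size but worth correcting, because the error could run only one way and there is no control group to offset it.

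**What to change.** In section 3.2, replace 80-180 with the declared outcome range of 70-180 mg/dL. State that percent time below 70, at 70-180 and above 180 mg/dL is computed in the same way from iPro and RT-CGM in all periods. Add the same boundaries to the outcome list in section 8.2.

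Recompute any baseline values already derived with 80-180, where the iPro readings were retained. Section 8.2 describes storage of RT-CGM, pump and meter data but does not mention iPro recordings, so their availability should be confirmed. If they were not kept, report the baseline figure with its own range and do not subtract it from the on-treatment value.

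The cost is a wording change and the rerun of one summary. This alters an analysis definition only; the glycemic targets in section 3.3 and the titration table in section 5.7 are untouched.
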